**Fig. 1 Fig1:**
[figure not shown]
Study design flow chart

Male and/or female patients will be randomized to either the HA (Synvic One®) treatment group (*n* = 27) or autologous fat (Lipogems®) treatment group (n = 27). To ensure enrollment goals are met, the investigator will draw from a waitlist of current patients that have expressed interest in participating in clinical trials. We also have IRB-approved flyers/brochures that will be shared with patients and nearby orthopaedic clinics (Additional file 1). Additionally, to improve adherence to the intervention protocol, participant who are allocated to the control group that complete all scheduled follow-up visits will be offered the adipose tissue treatment at the end of their final visit at no cost.

Since our primary aim is to estimate the effect size for future well-powered studies, we estimate the precision around which we can measure the effect. Based on a prior study using similar methods, but comparing WOMAC-A scores among patients receiving placebo to Hylan G-F (a joint lubricant) [54], we assumed standard deviations in the control and treatment groups of 0.66 and 0.67, respectively. With a sample size of 54 (27 per group), we will be able to estimate a two-sided 95% confidence interval within ±0.36 distance from the mean difference. For our secondary aim, we estimated the mean difference we would be able to detect, assuming a similar effect size for HA as was observed for Hylan G-F (μ = − 0.84, σ = 0.67) and found that we would have 80% power to detect a mean difference of − 1.4 in the autologous adipose group with a two-sided Type I error rate of 0.05.

Power was calculated using Pass 14 (Kaysville, UT).

At the treatment visit (day 0), patients will be randomly assigned to receive either a single intra-articular, ultrasound-guided injection autologous adipose tissue (6 ml) or a single intra-articular, ultrasound-guided injection of hyaluronic acid (6 ml). Patients with bilateral OA will be allowed to participate in this study, but only their more painful eligible knee will be treated (as determined by WOMAC-A). To control for possible responder differences between bilateral and unilateral symptomatic patients [55, 56], WOMAC-A for the contralateral knee will be obtained at baseline, 6 weeks, and 6 months (Table 1). If a participant has bilateral OA of equal pain intensity in both knees, the treatment knee will be selected randomly.

**Table 1 Tab1:** Study Calendar

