### Assignment of interventions

A random number sequence was generated using the Stata 14.0 uniform distribution. Blocks of four were used to ensure equal numbers of subjects in each group. To carry out the randomization of study subjects, we will utilize sequentially numbered, opaque, sealed envelopes. The statistician will prepare the envelopes for the Principal Investigator in order to maintain the concealment of the sequence prior to randomization. Upon enrolment in the trial, the next sequentially numbered envelope will be selected by the investigator and the subject will be offered the assigned treatment.

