Preliminary analyses will include descriptive statistics of basic demographic and clinical characteristics to assess the degree to which randomization was effective in balancing treatment groups. If any factors are found to have clinically significant differences, they will be considered and evaluated as possible confounders. The analysis will be by intent-to-treat. That is, all subjects will be analyzed according to randomization status, regardless of actual treatment received, compliance with therapy, or adherence to the study protocol. We will compare the outcome, difference in WOMAC-A score from baseline to 6 months, between the treated and untreated groups using generalized linear models (GLM) with a Gaussian family specified, assuming the data are normally distributed. If the data are not normally distributed, we will specify a more appropriate distribution based on an evaluation of the data via histogram. We will also use GLM to examine the relationship between the treatment and outcome at each time point at which the WOMAC was measured. Last, we will model the effect across all time points using a multi-level mixed effects model to account for repeated measures. Confounders will be defined as those variables that were found to differ between groups either at baseline or post-randomization and which, when added to the model, alter the effect estimate by > 15%. Potential a priori confounders include BMI, Bilateral vs contralateral OA, gender, ethnicity, and race. Potential interactions between treatment and visit will be evaluated. A *p*-value of <.05 will be considered statistically significant. The 29-point PROMIS® questionnaire will be evaluated using GLM at each measured time point and across time points using a multi-level mixed effects model, as described above. Missing data, if ≤5%, will be imputed using multiple imputation methods. Any covariate missing > 5% will not be included in the analysis.

A per-protocol analysis will also be conducted including only those participants who were protocol-adherent. Protocol adherence is defined as: (1) Receiving the assigned study treatment and (2) completing all follow-up visits. Lastly, sensitivity analyses will be conducted to assess the impact of using multiple imputation methods, if such methods are employed in the analysis.

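### The primary model's distribution may be replaced after looking at a histogram of the outcome data, with no criterion, family or link fixed, so the effect measure can depend on the data

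*Protocol article*

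**What the plan says.** The protocol article, section Data collection, management, and analysis, sets out the primary comparison: "We will compare the outcome, difference in WOMAC-A score from baseline to 6 months, between the treated and untreated groups". The model named for it is a GLM of the Gaussian family. The fallback comes straight after: should normality be judged to fail, "we will specify a more appropriate distribution based on an evaluation of the data via histogram". The section gives no test or threshold for judging normality, no list of families, no link function and no effect measure to report after a switch. The only sensitivity analyses named there concern multiple imputation. A per-protocol analysis is added, but it does not bear on the distribution.

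The sample-size text, under Participants, interventions, and outcomes, states the purpose: "Since our primary aim is to estimate the effect size for future well-powered studies". For precision it says "we assumed standard deviations in the control and treatment groups of 0.66 and 0.67, respectively" and concludes that "we will be able to estimate a two-sided 95% confidence interval within ±0.36 distance from the mean difference". The power statement for the secondary aim is also on the mean-difference scale, with -0.84 (SD 0.67) for HA and -1.4 for adipose tissue.

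On masking, participants are not blinded. The Discussion promises blinded analysis for the synovial fluid and fat measurements and does not mention WOMAC in that sentence. Under Assignment of interventions, "The statistician will prepare the envelopes for the Principal Investigator". The data section limits the statistician to de-identified data.

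**The concern.** The article does not merely leave a detail to a fuller document. It states a rule, and under that rule the look of the outcome data decides whether the planned primary model stands. Three things follow.

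- **The trigger is open.** A histogram with 27 patients per arm is a weak guide to shape, and two analysts could read the same plot differently. The Gaussian model concerns the distribution within arm, given treatment. The text does not say whether the plot is pooled, by arm or of residuals.
- **The replacement is open.** The usual GLM alternatives require positive or non-negative values, whereas a change score takes both signs. Using one needs a shift, a sign reversal or a new outcome definition, and each of these is a further unstated choice.
- **The effect measure is open.** With a log link the result is a ratio of mean changes, and the stated precision no longer applies to it.

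What is at stake is the trial's main product. Later studies are to be sized from its effect estimate, so the scale of that estimate should be fixed before the data are seen.

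**Working it through.** **Inputs** (all from the sample-size text): 27 per arm; SDs 0.66 and 0.67; HA change -0.84 with SD 0.67; adipose change -1.4; two-sided alpha 0.05. I read -0.84 and 0.67 as the mean and SD of the change, and use SD 0.67 in both arms for the sign check.

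**1. The plan's precision figure.** SE = sqrt(0.66²/27 + 0.67²/27) = sqrt(0.8845/27) = 0.181. Half-width = t(0.975, 52 df) × 0.181 = 0.363 (0.355 with the normal quantile). The stated ±0.36 is reproduced, and it belongs to the difference in means.

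**2. The plan's power figure.** With SD 0.67 and 27 per arm, the difference detectable with 80% power is 0.52 (noncentral t), and -0.84 - 0.52 = -1.36, which is consistent with the stated -1.4 after rounding. This too is on the mean-difference scale.

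**3. Sign of the outcome.** Under normality:
- HA: P(change ≥ 0) = P(Z > 0.84/0.67 = 1.254) = 0.105. Expected count 27 × 0.105 = 2.8; P(at least one of 27) = 1 - (1 - 0.105)^27 = 0.95.
- Adipose at -1.4: P(change ≥ 0) = P(Z > 1.4/0.67 = 2.09) = 0.018. Expected count 27 × 0.018 = 0.5.
- Chance that all 54 changes are strictly below zero: 3.0% under the planned alternative, 0.25% if both arms average -0.84.

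So a positive-support family would almost certainly be undefined for the change score as it stands, even after reversing its sign.

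**4. Effect measure.** With an identity link the planned contrast is -1.4 - (-0.84) = -0.56. With a log link on the reversed change it would be 1.4/0.84 = 1.67, a ratio to which ±0.36 does not apply.

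**5. Error rate of data-driven choice** (illustration: 20,000 null trials, 27 per arm; the alternative scale is the log of a shifted change; skewed data are a gamma with shape 2, rescaled to mean -0.84 and SD 0.67).

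| Rule | Normal data | Skewed data |
|---|---|---|
| Fixed t-test on the raw change | 4.7% | 4.8% |
| Scale chosen by a fixed normality test on pooled data | 4.6% | 5.0% |
| More favourable of the two results taken | 5.6% | 6.7% |

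A fixed selection rule hardly moves the error rate. Inflation appears only when the result guides the choice.

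**6. Effect of the remedy on the plan's figures.** Keeping the Gaussian mean difference leaves 0.363 and 0.52 unchanged. A rank test (assumed efficiency 3/π under normality) would have a detectable difference of about 0.53.

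**The case against.** The best defence is that the Gaussian model is the pre-specified default, the switch is conditional and openly published, and the trial is a small first step with efficacy testing as a secondary aim. Families and links are also details that a condensed article may leave elsewhere. The first part stands and limits the weight of the point. The last part does not remove it, because the article itself states that the distribution will be chosen from the data.

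Several stronger readings are tempting, and the document does not support them:

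- *No other distribution could hold the change score.* This is true only of the positive-support GLM families. A t or skew-normal error distribution can hold signed data, though none is named.
- *The result would become a ratio.* It could, but no link is stated, and an identity link would keep the difference.
- *The histogram is of the raw, pooled outcome.* The text says only that the data will be evaluated.
- *The statistician who prepared the envelopes will see the arms when choosing.* The document does not say who makes this choice or whether arm labels are visible. It is fair to say only that masking of the step is not described.
- *The choice is unregistered.* The registry record is not at hand, so this cannot be judged.
- *Non-normality does not matter at this sample size.* With the same shape in both arms, type I error of the two-sample t-test stays at 4.7% to 4.9%. With opposite-skew exponentials in the two arms it rose to 6.3%. For a shift of 0.77 SD, t-test against rank-test power was 80% against 94% (exponential), 79% against 91% (lognormal) and 79% against 89% (chi-square, 4 df). Efficiency can suffer, which is a reason for a planned companion test but not for an open switch.

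The 10.5% is itself computed under normality, while the fallback applies when normality is judged to fail. It illustrates the sign problem and does not estimate its size in that case.

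**Conclusion.** The point holds in a limited form. The rule lets the model for the primary comparison be replaced after the outcome data are seen, with the trigger, family, link and masking all unstated. Because the outcome is signed, the usual alternatives do not fit it without redefinition, and a non-identity link would abandon the scale on which both the aim and the ±0.36 are expressed.

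The size is moderate. The illustrated type I error inflation is 0.6 to 1.7 percentage points above 5%, and it needs result-picking; nothing in the document suggests that this is intended. The larger cost is an effect measure that is not fixed in a trial whose primary aim is to estimate an effect size. This rests on reading the stated -0.84 and 0.67 as the mean and SD of the change, on normality for the sign calculation, and on the simulated shapes described above. It should be corrected, but it does not undermine the design.

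**What to change.** Delete the sentence that allows the distribution to be chosen from a histogram. State that the primary estimate is the difference in mean WOMAC-A change from the Gaussian, identity-link model, whatever the shape of the data. Add a robust or bootstrap confidence interval if wanted. With equal arms and SDs of 0.66 and 0.67, HC3 standard errors are optional; in one check HC3 was slightly conservative under normality (4.6% against 5.0%).

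Pre-specify one sensitivity analysis for non-normality, either a permutation test or a rank-based comparison, and report it alongside the primary estimate and not in its place. A rank comparison does not estimate the mean difference, so it cannot stand in for the effect size. Plots of the distribution can remain as description.

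The cost is a change of wording and one extra analysis. Sample size, conduct and the stated precision are unaffected. The real downside is some efficiency forgone in the primary test if the data prove strongly skewed.

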Synovial fluid samples and excess adipose tissue will be analyzed to characterize the treatment and gain a better understanding of how adipose tissue affects the biochemical environment of the knee. To better monitor the disease progression and treatment efficacy, chemokines, cytokines, growth factors, and matrix metalloproteinases in the synovial fluid will be analyzed, including IL-1β, IL-6, IL-8, TNFα, C-terminal telopeptides of Type I collagen, and C-telopeptide of Type II collagen. The results will be made available for principle component analysis, which will be used to determine if pre-treatment synovial fluid inflammatory mediator and selected OA biomarker profiles that define different OA phenotypes predict the responses to autologous adipose tissue injections. The pro- and anti-inflammatory capabilities and cell viability of the autologous fat product will be evaluated and may also be compared to unprocessed preparations.

The use of NSAIDs may negatively impact healing [32, 63] and their prolonged half-life in synovial fluid allows them to accumulate in the joint [64], which is likely to impact synovial fluid biomarker profiles. To ensure that clinical outcomes, tissue healing and the biochemical profile of the synovial fluid are not influenced by the use of NSAIDs, participants will be asked not to take NSAIDs for at least 1 week prior to treatment and throughout the duration of the study.

Patients will be instructed to contact the study doctor before taking analgesic medications. Acetaminophen (250-500 mg) will be recommended if appropriate. The total number of days each patient takes acetaminophen will be logged and reported with published results. However, extended acetaminophen used will not be used as grounds for termination, as it has it is generally thought to have a clinically negligible effect on OA-related knee pain [65–67].

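### The confounder rule lets post-randomization variables into the treatment-effect model, so the adjusted estimate can be biased in either direction for the intention-to-treat effect

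*Protocol article*

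**What the plan says.** All the relevant text is in the Protocol article, mainly under Data collection, management, and analysis.

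- **Principle.** "The analysis will be by intent-to-treat", explained as: "all subjects will be analyzed according to randomization status, regardless of actual treatment received, compliance with therapy, or adherence to the study protocol".
- **Baseline screen.** After the descriptive comparison of the groups: "If any factors are found to have clinically significant differences, they will be considered and evaluated as possible confounders".
- **Confounder rule.** "Confounders will be defined as those variables that were found to differ between groups either at baseline or post-randomization". A second condition applies as well: including the variable has to shift the treatment estimate by more than 15%. Both parts must hold.
- **Candidates.** "Potential a priori confounders include BMI, Bilateral vs contralateral OA, gender, ethnicity, and race". The list is introduced as examples and does not close the rule.

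Several variables that treatment, or knowledge of the allocation, could influence are collected after randomization. For acetaminophen, "The total number of days each patient takes acetaminophen will be logged and reported with published results". WOMAC-A of the untreated knee is recorded at 6 weeks and 6 months (Participants, interventions, and outcomes). Table 1 and its footnote put weight and concomitant medications at every follow-up visit. Synovial fluid is aspirated again at both main follow-up visits. Participants are not blinded.

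**The concern.** Randomization removes confounding at allocation. A between-arm difference that arises later cannot be a common cause of allocation and outcome, so it is not a confounder of the randomized comparison. If treatment caused it and it lies on the path to pain, adjusting for it subtracts part of the effect. If it shares an unmeasured cause with pain, adjusting for it creates an association that treatment did not produce.

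The 15% criterion gives no protection, because mediators and colliders are variables that move the estimate. The baseline screen and the rule's own baseline limb already cover baseline imbalance, so the only thing the post-randomization limb adds is variables measured after allocation.

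The stated primary aim is to estimate the effect size for future trials. A shift in that estimate would pass directly into the next trial's sample size.

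**Working it through.** **1. The plan's own figures.** Inputs from Participants, interventions, and outcomes: 27 per group, SDs 0.66 and 0.67, two-sided alpha 0.05, HA mean -0.84, adipose mean -1.4 at 80% power.

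- 95% CI half-width = t(0.975, 52) × √(0.66²/27 + 0.67²/27) = 0.363. The plan says 0.36, so it reproduces.
- Detectable difference at 80% power with SD 0.67 (noncentral t) = 0.521. This gives an adipose mean of -0.84 - 0.52 = -1.36, which rounds to the plan's -1.4.

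The true difference used below is therefore -0.52.

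**2. Bias if the variable is always adjusted for.** Assumptions that are not in the documents: treatment shifts a post-randomization variable by 0.5 SD, and its within-arm correlation with pain change is 0.4.

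- Change in estimate = shift × correlation × outcome SD = 0.5 × 0.4 × 0.67 = 0.134.
- Expected adjusted estimate = -0.52 + 0.134 = -0.386, an attenuation of 0.134/0.52 = 26%.
- By simulation: estimate -0.39, power 59%, null rejection 12%.

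This is the ceiling for the scenario, because the rule does not admit the variable in every trial.

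**3. The two-part rule as written.** The variable enters only if it differs between arms and moves the estimate by more than 15%. The plan does not define when a variable differs, so it is taken as p<0.05 and, more loosely, p<0.20. Simulated results for the same scenario:

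| | Unadjusted | Rule, p<0.05 | Rule, p<0.20 | Always adjusted |
|---|---|---|---|---|
| Variable enters (true -0.52) | – | about 41% | about 63% | 100% |
| Mean estimate (true -0.52) | -0.52 | about -0.44 | about -0.41 | -0.39 |
| Power | 80% | about 66% | about 60% | 59% |
| Variable enters (null) | – | about 43% | about 70% | 100% |
| Null rejection | 5% | about 7% | about 10% | 12% |
| Mean estimate, opposite shift | -0.52 | about -0.61 | about -0.64 | -0.65 |

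Under the rule the estimate moves by 0.08 to 0.11, which is 15% to 21% of 0.52 and 22% to 31% of the planned half-width of 0.36.

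**4. Range over other assumptions**, with both criteria applied and p<0.05:

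- *Mediator*: true effect -0.56, shift 0.5 to 1.0 SD, outcome slope 0.20 to 0.335 per SD. The variable enters in 33% to 95% of trials, the mean estimate is -0.50 to -0.24, and power falls from about 86% to between 76% and 26%.
- *Shared unmeasured cause, no true effect*: shift 0.5 to 1.0 SD, correlation of the variable with that cause 0.5 to 0.7. The mean estimate is -0.06 to -0.32 instead of 0, and type I error is 6% to 43%.
- *Shared unmeasured cause, true effect -0.56*: the mean estimate is inflated to between -0.61 and -0.88.

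**5. With the limb removed.** Without post-randomization variables the same simulations are unbiased (-0.56 for a true -0.56, about 0 under the null) and reject in about 5% of null trials. Sample size and planned precision do not change.

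**The case against.** The strongest reply is that the rule was meant for baseline characteristics. All five named candidates are of that kind, acetaminophen days are to be logged and reported and are nowhere named as a covariate, and an unseen analysis plan may narrow the rule. The candidates do show what the authors had chiefly in mind. But the list is open, the text names the post-randomization limb explicitly, and nothing restricts it. Even BMI could be taken from follow-up, since weight is measured there. This is a rule the article states, not a detail it leaves out.

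Other objections stand in part and limit the point:

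- A reader might infer that the randomized comparison is biased outright. The documents do not support that. A treatment-affected variable must meet both criteria, and some post-randomization differences will be chance.
- A reader might take the 26% attenuation and 12% type I error as the rule's behaviour. They describe adjustment in every trial.
- A reader might infer a contradiction with intention-to-treat. The article defines that as analysis by randomized group, which covariate adjustment does not breach. The problem is that the adjusted coefficient may estimate something other than the effect of assignment.
- A reader might treat the 15% rule as an equal fault, because it is a relative threshold and unstable near zero. In a simulation with five baseline covariates and no true effect, at least one passed the 15% part alone in 84-90% of trials. Requiring also a difference at p<0.05 reduced this to about 18%. Baseline-only selection kept type I error at about 5%.

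**Conclusion.** The point holds in a limited form. As written, the rule permits adjustment for variables that treatment may have changed, and the resulting estimate can be biased in either direction for the effect of assignment. This follows from the text and needs no assumption. Its size does need assumptions: the shift, the correlation with pain change and the meaning of differing between groups are not in the documents. In the moderate illustration the effect is understated by about 15-21% or, with the opposite shift, overstated by about 17-23% (0.09/0.52 to 0.12/0.52). Stronger assumed relations give larger distortions. The part that must change is the post-randomization limb. The 15% criterion applied to baseline variables alone is a weaker choice than fixed adjustment, not a source of inflated type I error.

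**What to change.** **Required.** In the confounder definition, delete the words that admit post-randomization differences, and state that only variables measured before randomization can be covariates in a model for the treatment effect. Report acetaminophen days, follow-up contralateral WOMAC-A, follow-up weight and synovial markers descriptively by arm, or in an analysis labelled exploratory. The cost is a wording amendment, made before outcome data are compared by arm. Data collection and sample size are unaffected.

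**Secondary.** Replace the 15% change-in-estimate rule with a short fixed list of baseline covariates that includes baseline WOMAC-A, and show the unadjusted estimate beside the adjusted one. The cost is a few degrees of freedom. The gain is modest: in the five-covariate simulation, power was about 86% with fixed adjustment against 83% with selection and 80% unadjusted. Which other baseline covariates to include is the sponsor's choice.

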### Data collection, management, and analysis

Demographics and survey data will be stored using a REDcap database created specifically for the purpose of this study. REDcap has several security features, including off-site backups, an audit trail, secure logins, de-identified data exports, and built-in filtering methods to ensure data quality. Additionally, survey answers (clinical outcome data) will be directly entered into the database by the participants via iPad before they interact with the examining physician. Documentation not included in the quantitative analysis of clinical outcomes will be recorded using traditional source documents (Additional files 2 and 3). These documents will be kept in the participant’s binder and locked in a secure location. All data collection will take place in the clinic.

Only those who require access to the database will be given access. Coding of the variables will be done within the database. A completed data file will be stored by the statistician in the shared folder for the Clinical Translational Science Institute Biostatistics core at USC and will be backed up regularly. The statistician’s access to the database will be limited to de-identified data. Data quality will be assured by range checks for unusual or impossible data values. Data management will include a thorough data cleaning (checking ranges, evaluating distributions) and deriving of variables needed for analysis.

All protocol deviations will be recorded. The same outcome data will be obtained from all participants, regardless of protocol adherence. In order to promote retention and compliance, participants that receive the HA treatment and complete all schedule follow-up visits will be offered the fat treatment at the 6-month (final) follow-up visit at no charge. Imputation will be used if loss to follow-up is uncommon.

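### Multiple imputation is allowed only up to 5% missing, so the 6-month WOMAC-A GLM loses its missing-data handling, and its only missing-data sensitivity analysis, just as losses start to matter

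*Protocol article*

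**What the plan says.** All of the relevant rules are in the protocol article, Data collection, management, and analysis.

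- **Imputation rule.** "Missing data, if ≤5%, will be imputed using multiple imputation methods". The paragraph on retention gives a matching rule in words: "Imputation will be used if loss to follow-up is uncommon". Because the second sentence is about loss to follow-up, the rule covers outcomes and not only covariates.
- **Above 5%.** The one stated action is to leave out any covariate with more than 5% missing. Nothing is stated for outcomes.
- **Sensitivity analysis.** "sensitivity analyses will be conducted to assess the impact of using multiple imputation methods, if such methods are employed in the analysis".
- **Models.** The first comparison listed is a Gaussian GLM on the baseline to 6-month WOMAC-A change. GLMs at each visit follow, and then a multi-level mixed model over all time points. None is designated primary by name. The Injection procedure section describes the primary outcome as average WOMAC-A change over time.
- **Analysis set.** The analysis is by intent-to-treat: "all subjects will be analyzed according to randomization status". A per-protocol analysis is restricted to participants who received the assigned treatment and attended every follow-up visit.
- **Retention.** HA participants who complete all visits are offered the fat procedure free of charge. The fat arm has no matching offer.

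**The concern.** Imputation has little to do when one or two values are missing and more to do as the number grows. The plan permits it in the first situation and withdraws it in the second. A GLM on the 6-month change needs a month-6 score from each participant. Once imputation is switched off, anyone without that score drops out of the model unless some other method is specified, and none is. The set analysed then moves towards the per-protocol set, which also requires complete follow-up, so comparing the two analyses tells the reader less.

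The check on missing data is tied to the same switch and is absent in the range where a reader would most want it.

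What is at stake is the trial's main product, an effect size for planning later studies. Participants know their treatment, the outcome is self-reported pain, and only one arm has a reward for completing follow-up. Loss that differs by arm and relates to response is therefore plausible, although the article gives no evidence that it will occur.

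**Working it through.** **Inputs from the protocol article.** 54 participants, 27 per group; "standard deviations in the control and treatment groups of 0.66 and 0.67, respectively"; a stated 95% confidence half-width of ±0.36; an imputation ceiling of 5%. No expected loss rate is given, so the loss rates below are assumptions, shown as a range.

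**1. The plan's own precision figure.** The article says "we will be able to estimate a two-sided 95% confidence interval within ±0.36 distance from the mean difference".

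Half-width = t(0.975, 52) × √(0.66²/27 + 0.67²/27) = 2.007 × 0.181 = 0.363. The normal version is 1.96 × 0.181 = 0.355. The stated 0.36 is reproduced.

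**2. Where the ceiling falls.** 0.05 × 54 = 2.7.

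| Counted over | Last count with imputation | First count without |
|---|---|---|
| 54 month-6 scores | 2/54 = 3.7% | 3/54 = 5.6% |
| 27 in one arm | 1/27 = 3.7% | 2/27 = 7.4% |
| 108 follow-up scores (54 × 2 visits) | 5/108 = 4.6% | 6/108 = 5.6% |

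The article does not say which denominator applies. The rest uses the first row.

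**3. Chance of passing the ceiling.** P(X ≥ 3) with X ~ Binomial(54, p):

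| Assumed individual loss p | Expected losses | P(3 or more) |
|---|---|---|
| 3% | 1.6 | 22% |
| 5% | 2.7 | 51% |
| 10% | 5.4 | 92% |
| 15% | 8.1 | 99% |

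**4. Cost in precision.** The formula of step 1, with losses split as evenly as possible between arms:

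| Lost | Analysed | Half-width |
|---|---|---|
| 0 | 54 | 0.363 |
| 3 | 51 | 0.374 |
| 5 | 49 | 0.382 |
| 8 | 46 | 0.395 |

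Three losses widen the interval by 0.374 − 0.363 = 0.011, which is small.

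**5. Illustration of bias.** Suppose k of 27 in one arm are lost, none in the other, and those lost differ from those retained by D points on average. The completers' mean is then off by (k/27) × D.

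| k | D = 0.5 | D = 1.0 |
|---|---|---|
| 3 | 0.06 | 0.11 |
| 5 | 0.09 | 0.19 |
| 8 | 0.15 | 0.30 |

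With k = 4 and D = 0.67 (one SD), the shift is (4/27) × 0.67 = 0.099, and 0.099/0.363 = 27% of the planned half-width. These values of k and D are assumed and unfavourable, since all losses are placed in one arm. They show how bias scales with loss.

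**The case against.** Several points on the other side stand, and they limit the finding.

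- **A mixed model is already planned.** If fitted by likelihood, it keeps a participant with a week-6 but no month-6 score at any missing rate, and it is valid if data are missing at random. A reader might infer that the whole intent-to-treat analysis turns into a complete-case one. The article does not support that. The problem is confined to the 6-month GLM and the per-visit GLMs. The description of the primary outcome as change over time fits the mixed model at least as well as the GLM.
- **Completers-only analysis is an inference.** No method is named for outcomes missing above 5%. Dropping those participants is what a GLM does by default, and a separate analysis plan, not shown, could say otherwise.
- **No contradiction with intent-to-treat wording.** A reader might set "all subjects will be analyzed according to randomization status" against the loss of participants. The rest of that sentence concerns treatment received, compliance and adherence. It fixes the arm in which a participant is counted and says nothing about missing outcomes.
- **The third loss is one reading.** Per arm the ceiling is passed sooner, and over all follow-up scores later.
- **The 0.10 shift is not the cost of the rule.** Imputation under missing at random would remove only the part that baseline and week-6 scores predict.
- **Differential loss is conjecture.** The free procedure is offered to improve retention, and the article intends to collect the same outcomes whatever the adherence.
- **Some check remains.** Comparing the GLM with the mixed model shows sensitivity under missing at random. No missing-not-at-random analysis is stated.

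None of this defends the ceiling itself. It is stated twice and runs in the wrong direction, so it is a badly fixed rule and not a detail left for later.

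**Conclusion.** The point holds for the GLM on the 6-month WOMAC-A change and for the per-visit GLMs. The plan withdraws imputation, and the only stated missing-data sensitivity analysis, once missingness exceeds 5%, and puts nothing in their place for outcomes. Counted over 54 participants, that happens at the third missing month-6 score. At an assumed individual loss of 5% this is about an even chance (51%); at 10% it is likely (92%).

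The harm at exactly three losses is small. It lies in bias that may grow with further losses, and its size cannot be fixed from the article. The conclusion rests on three assumptions: the 5% is counted over participants for the month-6 outcome, a GLM without imputation drops participants who lack the score, and no unseen document states another method. The unaffected mixed model softens the problem but does not settle it, because it comes last in the list and is not designated primary. This should be fixed before outcomes are seen; it does not invalidate the design.

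**What to change.** 1. Remove the 5% ceiling on imputing outcomes, together with the sentence that ties imputation to uncommon loss.
2. Choose one of two routes and state it as primary. Either designate the mixed model already planned, fitted by likelihood to all observed WOMAC-A values with the month-6 between-arm contrast as the estimate, or keep the 6-month GLM with multiple imputation by arm, including week-6 scores, at any missing rate.
3. Run one missing-not-at-random sensitivity analysis, for example delta-adjusted, whether or not imputation is used.
4. As a lesser point, fill in missing baseline covariates by a simple method instead of dropping any with more than 5% missing. The named candidates (BMI, laterality, gender, ethnicity, race) are baseline items at one clinic, so this will seldom arise.

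The cost is a change of wording and a little more programming. No new data are needed.
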